### Intervention

CANreduce 2.0 is an automated web-based self-help tool developed by the Swiss Research Institute for Public Health and Addiction (ISGF) to reduce cannabis consumption in problematic cannabis users [26]. It has three main components: a dashboard, a consumption diary, and eight modules designed to reduce cannabis use using the principles of motivational intervention, self-control practices, and cognitive behavioural therapy (see Table 3). Participants can study all the modules at their own pace and in whatever order they choose, though a specific order is advised.

**Table 3 Tab3:** Brief description of the eight intervention modules (For further information, please see Amman [25] and Baumgartner [26])

**Module**	**Brief objective description**	**Therapeutic base**
**1 Introduction**	General overview and introducing the fictional companions	Motivational interviewing (MI) techniques [27]
**2 Identifying risky situations**	Identify personal risk situations and increase awareness of irrelevant decisions that could lead to cannabis use	Cognitive behavioural therapy (CBT) approach to relapse prevention [28]
**3 Working on needs**	Learn skills to strengthen social contacts, decrease possible ruminations, and develop healthier sleeping habits	Behavioural activation approach [29]
**4 Craving**	Learn strategies to deal with craving	CBT principles [30]
**5 Dealing with relapses**	Learn skills for relapse prevention	Cognitive behavioural therapy (CBT) approach to relapse prevention [28]
**6 Working on problems**	How to deal with common problems using new problem-solving skills	Social problem-solving approach [31]
**7 Saying “No”**	Strengthen refusal skills	CBT principles [30]
**8 Preserving achievements**	Review the work done and create a personalized list of points to secure achievements made	MI techniques [27]

Since CANreduce 2.0 is considered a medical device, because of the European Union guidelines 93/42/EWG and 2007/47/EWG, its conformity has been assessed, and all potential risks have been evaluated.

### Active study arms

Both active study arms have the enhanced version CANreduce 2.0 with social presence that is described in Amann and Baumgartner [25, 26]. Psychological support (feedback on demand) is only present in study arm 1 and includes offering participants the opportunity to contact an e-Coach via the platform’s internal messaging system (Fig. 2) or by e-mail. As such, they can receive psychological support when needed, though it will only take place on their initiative. Within two workdays, the participants will receive personalized written feedback. Both active treatment arms (study arms 1 and 2) will have access to the following elements of the CANreduce-SP program (for a detailed description of the content of each element, please review Amann and Baumgartner [25, 26]):

**Fig. 2 Fig2:**
[figure not shown]
Dashboard for study arms 1 and 2 (translated from Spanish to English for publication purposes only)

#### Welcome page

Before accessing the restricted area, users are introduced to the welcome page, which has a short, written description of the study and an introductory video in which the e-coach [name] introduces herself and gives a general overview of CANreduce highlights and objectives. Both the written description and the video aim to motivate visitors to ask for more information about the study and how to enrol by clicking the inscription button that leads to the registration and consent procedure explained above.

#### Dashboard

The dashboard (see Fig. 2) works as the main page of the program. All the practical information is displayed clearly and briefly, including a chart with expected and actual consumption within the program, indicators of up-to-date progress on the intervention modules, and a weekly calendar to record cannabis consumption over the preceding week. The Message button at the top right of the screen only appears in the intervention group with psychological support (arm 1).

#### Self-help intervention modules

The intervention modules (Table 3) are the same for both active intervention groups (arms 1 and 2). They are accessible from the very beginning, both on the intervention website's main menu page (see Fig. 3) and on the dashboard (see Fig. 2). It is recommended that users complete the modules sequentially at a pace of one or two per week; however, participants are free to proceed at their own pace, complete modules in whatever order they please, and repeat any modules they consider particularly helpful or essential.

**Fig. 3 Fig3:**
[figure not shown]
Module overviews (translated from Spanish to English for publication purposes only)

#### Fictional companions

Six fictional companions were created to accompany users during the program. Certain questions have been identified that are commonly asked by users at crucial points in each module. These companions are intended to help participants overcome their doubts dealing with these questions and situations, by providing them examples of what they themselves did, thereby encouraging study participants to reflect and share their own thoughts and experiences.

#### Consumption diary

All users are required to define their standard joint to activate the registration process. The configuration includes (1) the type of cannabis (indoor, outdoor, resin); (2) if it is blended with tobacco or not; and (3) the amount they use ranging from 67 to 500 mg. All possible configurations are represented with a photo to provide automatic visual feedback to fit the user’s standard joint. The individual’s standard joint cannot be changed once this step is completed. Creating this personalized standard unit helps users to record their target of weekly consumption and actual consumption over the preceding week.

#### Extra elements

The program contains several complementary resources through the menu on the top bar. In “Data of interest,” neutral information about cannabis is provided, from its mechanism of action and effects on the brain and consciousness to issues related to Spanish legislation. In the section “Your activities,” users can plan weekly events as alternatives to consumption situations. They can then compare their initial expectations with the experience itself, thereby potentially encouraging them to repeat positive experiences. In the section “Help,” participants can access both the CANreduce-SP instructions and the specific resources for urgent help to find out what to do in case a crisis arises (nearby care centres and recommendations to overcome moments of crisis). Finally, in the “My profile” menu, they can access their annotations and summarize the personal contributions and strategies that each user has established in the program’s modules.

#### Automated motivational feedback

Active intervention group participants are encouraged to fill out their consumption diary at least once every week via a reminder e-mail. This process promotes goal-setting (Mohr’s accountability factor) and tests and improves self-efficacy without the self-deception usually seen in a professional therapy setting. Additional e-mails can be sent out automatically or triggered by an investigator if certain conditions arise (e.g. not completing the consumption diary, stalling, increasing cannabis consumption, or underutilizing program resources). Regarding automatic e-mails, the only difference between the active arms is the addition of the paragraph encouraging participants to initiate contact for psychological support (feedback on demand) that was added to study arm 1 (see Table 4).

**Table 4 Tab4:** First-week e-mail example (translated from Spanish to English for publication purposes only)

Study arm 1 and 2 (paragraph in italics ONLY appears in study arm 1)
Hello {participant’s name }! You've made it through the first week. Congratulations! I hope you've been well these past few days. Your second week starts tomorrow. Log in today or late in the afternoon at https://www.CANreduce.es and record in your user diary how much cannabis you have consumed in the last few days. You can also add when and how much cannabis you would like to use next week. I take this time to encourage you to start another one of the eight modules. If you do the modules, you will get the most out of the course and achieve your goals. *Remember that if you need my opinion about your proposals or ideas or want me to help you with any of the exercises, you only have to send me an e-mail explaining what you want. Just indicate which exercise on which you need my help or opinion. I will answer you within 48 hours on work days.* Go for it, and happy week! Your e-coach [name]

#### Psychological support

Several elements of human support increase adherence (e.g. accountability to a coach who is considered trustworthy) [32]. As explained by Mohr\s supportive accountability, human support may be provided by a wide range of trained individuals [33]. The feedback received does not directly influence the treatment’s effectiveness but is more a strategy to highlight human support during the process. The goal is to increase confidence in the trainer and a sense that the trainer is concerned with the participant’s interests [33, 34]. This strategy increases the perception of legitimacy that would encourage people to respond to adherence demands actively. We provide automated human support through e-mails, videos, and reminders to both active groups. Besides this, we offer psychological support (feedback on demand) via personal contact with the e-coach to ask questions or express concerns via the internal message system or e-mail to increase this human support effect and evaluate the level of demand for this service.

#### Control condition

The control condition will be treatment as usual (TAU). Participants will be informed about this group's relevance, their path in the study (Fig. 1) and the link to the Plan Nacional Sobre Drogas (National Drug Plan) web page to find information about the drug treatment centre nearest their place of residence. During the 3-month assessment at (*t*_2_), as with the two active intervention groups (study arms 1 and 2), TAU group participants will be asked if they have used other treatments during their study participation and what they were. Then, they will be reallocated into intervention group 2 (study arm 2) to access all the CANreduce resources, except psychological support, and will have their last assessment (t_3_) after this 6-week program.

#### Technical specifications

CANreduce-SP is based on the Swiss Program CANreduce 2.0 [25, 26], which was programmed and developed using the content management system Drupal 7 and a MySQL database. All access to the study website CANreduce.es [35] is encrypted and password-protected using the secure sockets layer (SSL) protocol. Only participants will have access to any data they have previously entered online on their own. Data validation and mandatory fields on website boxes are enabled to prevent logical errors or data missing in the study database. The webpage has a responsive design to adapt to any portable device automatically. Completing the registration process requires potential users to have a valid e-mail and activate checkboxes pertaining to the essential ethical and responsible aspects of the study (see Tables 1 and 2). All data will be stored on a server hosted by an external provider that meets the IT security outsourcing regulations of the European GDPR 2016/976. Final data will be extracted from the database using Drupal and phpMyAdmin. The data will then be stored at the principal investigator’s institution on local computers for further processing and local file servers for archiving. All participants’ personal data will be deleted after their participation in the study and will never be published or presented at scientific meetings. Anonymized study data will be available upon request. The investigator affirms and upholds the principle of every participant's right to privacy and that all personnel involved in the study will comply with applicable privacy laws.

### Measurements

All data will be retrieved online. Sociodemographic data will include subject gender, age, autonomous community, education level, and work status. The primary outcome will be the number of days of cannabis use over the preceding seven days, according to the Time-Line-Follow-Back (TLFB) method [36, 37]. The TLFB is a calendar used in many studies to obtain estimates of the quantity of daily drug use (alcohol, cannabis, cocaine…). It is broadly recommended to be used for outcome evaluation and treatment planning purposes.

Secondary outcomes will include the number of days of cannabis use over the last 30 days, again using the TLFB method, and the number of standardized cannabis joints [24] consumed in the previous week. The presence of a cannabis use disorder (CUD) will be measured by the CUDIT-R (Cannabis Use Disorder Identification Test-Revised, CUDIT-R) [38], a validated and quick-to-use self-administered questionnaire with eight items that has been found to exhibit excellent psychometric properties. Questions 1–7 are scored on a 0–4 scale (range 0–28), and question 8 is scored 0, 2, or 4 (total range score 0–32). Participants scoring 8 or more may have hazardous cannabis use, while scoring 12 or more indicates potential cannabis use disorder. The Severity Dependence Scale (SDS) [39, 40] was added to assess the severity of cannabis use disorder. It has five items scored on a 4-point scale (0-3) with a total range score of 0 to 15, where higher scores denote worse severity. The Alcohol Use Disorders Identification Test (AUDIT) [41, 42] was developed by the World Health Organization (WHO) to assess alcohol consumption and alcohol-related problems. Each of the 10-items is scored 0–4, with a total score ranging from 0 to 40. Scores of 8 or more suggest hazardous or harmful alcohol use. Anxiety and depression are assessed with PROMIS (Patient-Reported Outcomes Measurement Information System). PROMIS is a set of person-centred measures that evaluate and monitor physical, mental, and social health in adults and children. It can be used within the general population and among individuals living with chronic disorders. It was developed and has been validated with state-of-the-science methods to be psychometrically sound and to transform how life domains are measured. Both the PROMIS Emotional Distress - Depression - Short Form 8b and the PROMIS Anxiety 8a - Adult v1.0 have eight items; each scored using a Likert scale ranging from 1 to 5, with total scores ranging from 8 to 40. [43, 44]. In both instruments, higher scores imply worse outcomes. Quality of life is assessed with EQ-5D-5 L, known for being an excellent, self-administered, health-related quality of life questionnaire [45]. The scale measures quality of life across five domains: mobility, self-care, usual activities, pain/discomfort, and anxiety/depression. Total scores range from less than 0, where 0 is the value of a health state equivalent to dead; negative values represent values worse than death (i.e. a life that an individual considers not worth living due to, for example, intractable, intolerable pain), and 1 indicates full health. The second part of the questionnaire consists of a visual analogue scale (VAS) on which the patient rates his/her perceived health from 0 (worst imaginable health) to 100 (best imaginable health).

At the 3-month follow-up assessment (*t*_2_), any adverse effects will be identified using Rozental’s Negative Effects of Internet Interventions [46]. Finally, all participants will be asked if they have used any treatment other than CANreduce-SP during their participation in the program. If so, we will ask them to describe the treatment they used. Data on webpage usage (i.e. number of completed modules, time spent on the website) will be collected as an indicator of treatment adherence. These data could help to identify ways to optimize CANreduce-SP to decrease attrition rates.

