## Methods/design

The Spanish version of the adherence-focused, guidance-enhanced, web-based self-help program CANreduce 2.0 (CANreduce-SP) will be evaluated within a three-arm RCT, in which the effectiveness of CANreduce-SP with psychological support and CANreduce-SP without psychological support will be compared against each other and against treatment-as-usual (TAU) at reducing cannabis use in problematic users. Given that the study will only be partially single-blinded, the two active intervention arms will be neutrally described to subjects assigned to those arms to prevent participants from preferring one over the other. However, participants assigned to TAU will immediately be made aware of their group. As for study personnel, though any who directly provided support to program users cannot feasibly be blinded to subjects’ group assignments, all other study personnel (e.g. those involved in data collection, editing and analysis) will be. Co-occurring mental health symptoms will be screened with the rest of the primary and secondary outcomes during the baseline assessment (*t*_0_) to ensure that all potential participants meet study criteria and are eligible to be randomized and allocated to one of the three study conditions. Further assessments will take place 6 weeks after baseline, which is also the time when participants will have completed the 6-week program (*t*_1_), as well as at 3 months (*t*_2_), and 6 months (*t*_3_) follow-up (Fig. 1). Having 6 months of follow-up will allow us to examine the durability of any changes achieved with either of the two active interventions (study arms 1 and 2). For ethical reasons, we have elected not to ask study participants in the TAU group to wait a full 6 months for their final follow-up. Instead, we will grant them access to the intervention group without psychological support (study arm 2) 18 weeks after baseline—6 weeks after their 3-month evaluation (*t*_2_)—with the intention of assessing any response to the program they might have had at the 6-month follow-up assessment (t_3_). In this way, they will provide the study with a further, cross-over comparison.

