### Randomization and trial flow

Once participants have completed their baseline assessment (*t*_0_), they will be randomized by a computer algorithm in a 1:1:1 ratio into one of three parallel groups and will be registered automatically in the background database. Participants’ internet protocol (IP) address will be monitored to prevent multiple registrations from one user attempting to have more than a single account or be allocated to a different group than originally assigned. Participants assigned to the control condition (TAU/study arm 3) will be remitted to a list with the treatment centres nearest their postal code. After 3 months in TAU, participants will gain access to CANreduce-SP without psychological support. The four assessment points of the study are depicted in Fig. 1. All subjects will be asked about their potential for using some different treatment during their participation in the study. A reminder e-mail will be sent before each assessment. It will contain information about the value of their answers, the estimated length of the questionnaire (in time to complete), and compensation for each evaluation to enhance the response rate. The same e-mail will be sent if there is no answer within 2 days and again after 4 days. One week after the last e-mail, participants will be contacted by phone and will be offered the option of completing the follow-up questionnaire verbally with an interviewer. Participants who drop out will be asked to answer a few questions pertaining to the two the primary outcomes and why they have decided not to continue in the study. Inactivity will not be considered a dropout criterion, due to the breaks that participants of web-based interventions commonly take. It is expected that some of these users will re-join the program later. A participant’s active withdrawal from the study will be the only dropout criteria. If possible, all data already gathered from these participants will be analysed. Figure 1 depicts the flow of subjects through the study.

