### Sample size calculation

Anticipating that a Cohen’s *d* of 0.40 would be realistic to determine effect size differences on the primary outcome between groups, based on previous study experiences [23–26], a sample size of *n* = 100 in each study group would have 80% power on two-tailed *t*-test calculations performed using G*Power software (Faul, Kiel) and an alpha error of 5%. Given an average attrition rate of 50% in online studies involving cannabis misusers [26], our final adjusted sample size is *N* = 450.

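### The negative-effects questionnaire is scheduled only at 3 months, before any treatment-as-usual participant can use the programme, so those who use it later have no stated harm measure after exposure.

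*Protocol article*

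**What the plan says.** The Measurements section of the protocol article states: "At the 3-month follow-up assessment (*t*_2_), any adverse effects will be identified using" a published negative-effects instrument for internet interventions. It names no other time point and does not say which arms complete it.

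The article dates TAU access to the programme in three ways:

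- Methods/design: "we will grant them access to the intervention group without psychological support (study arm 2) 18 weeks after baseline", which it describes as 6 weeks after the t2 evaluation.
- Randomization and trial flow: "After 3 months in TAU, participants will gain access to CANreduce-SP without psychological support".
- Control condition, directly after describing the t2 assessment: "Then, they will be reallocated into intervention group 2 (study arm 2) to access all the CANreduce resources".

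Methods/design gives the purpose of this delayed access: it is offered "with the intention of assessing any response to the program they might have had at the 6-month follow-up assessment" (t3), as a further cross-over comparison.

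The Sample size calculation section supplies the attrition figure: "Given an average attrition rate of 50% in online studies involving cannabis misusers", the total is set at 450. Randomization and trial flow describes e-mail reminders followed by a phone call with the option of answering verbally. It counts only explicit withdrawal as dropout, and it asks those who withdraw about the primary outcomes and their reasons for leaving. The Data analysis section says that there will be no independent data monitoring committee and no formal stopping rules, because the intervention is regarded as low risk.

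**The concern.** A harm measure should follow the exposure it is meant to describe. Here the only stated administration comes before one arm's exposure. The plan intends to learn about response to the programme from TAU crossovers at t3, yet it schedules no matching question about negative effects at that visit.

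In the active arms the timing is late rather than absent. The programme ends at t1, which is already an assessment, but negative effects are first asked about at t2, after further loss to follow-up is possible. If people who had a bad experience are less likely to answer at t2, the reported frequency would be too low. With no monitoring committee, this questionnaire is the only instrument described in the article that is dedicated to negative effects of the programme, so its coverage largely determines what can be said about harm.

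**Working it through.** **1. Order of events.** By the Methods/design arithmetic, t2 falls at week 18 − 6 = 12. The active arms finish the 6-week programme at t1, so their questionnaire comes 12 − 6 = 6 weeks after programme end. For TAU:

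| Statement of TAU access | Access relative to t2 | Negative-effects measure after access |
|---|---|---|
| Methods/design | 6 weeks after | none stated |
| Randomization and trial flow | at 3 months | none stated |
| Control condition | directly after | none stated |

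The three statements disagree, but the conclusion is the same under each: the only assessment after TAU exposure is t3, where no negative-effects measure is listed.

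**2. The plan's sample size.** For d = 0.40, two-sided 5% and 80% power, the exact t-test needs 99.1 per group. The stated 100 per group gives power 0.804, so that figure reproduces. The total of 450 does not follow from 50% attrition: 100 / (1 − 0.5) = 200 per arm, or 600. It equals 100 × (1 + 0.5) = 150 per arm, which leaves 100 per arm only if the loss is 1 − 100/150 = 1/3. Both loss rates are therefore carried below.

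**3. Who is scheduled to be asked.** Here exposed means randomised to arm 1 or 2 (2 × 150 = 300), plus X TAU participants who later use the programme, with X between 0 and 150. The share due to be asked while already exposed is 300 / (300 + X), which runs from 300/450 = 67% to 300/300 = 100%. The share never scheduled after exposure is X / (300 + X), at most 150/450 = 33%.

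**4. Who would give data.** With loss d by t2, the share is 300(1 − d) / (300 + X).

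| TAU participants who later use the programme | d = 50% | d = 1/3 |
|---|---|---|
| All 150 | 150/450 = 33% | 200/450 = 44% |
| Retained TAU only (75; 100) | 150/375 = 40% | 200/400 = 50% |
| Half of those retained (37.5; 50) | 150/337.5 = 44% | 200/350 = 57% |
| None | 150/300 = 50% | 200/300 = 67% |

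A majority of exposed participants would give no data at d = 50% as soon as any TAU participant crosses over. At d = 1/3 this requires 200 / (300 + X) < 0.5, that is X > 100.

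The Recruitment section gives a required sample of 300 rather than 450. With 100 per arm the percentages are unchanged.

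**5. What a t3 repeat would add.** At 50% retention, up to 75 TAU crossovers would answer: (150 + 75)/450 = 50% instead of 33%, or 225/375 = 60% instead of 40%.

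**The case against.** A reader might infer that most exposed participants are never asked. The article does not support that. All 300 active-arm participants are due at t2 and are pursued by e-mail and phone. Vouchers reward completion, and inactivity is not dropout. Not answering is different from not being asked, and at least two thirds of those exposed are scheduled to be asked.

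A reader might also infer that half the active-arm participants will be gone by t2. The 50% is an average from other online studies, with no time point or arm attached. The 33% coverage figure is the low end of the range, since it pairs 50% loss in the active arms with every TAU participant later using the programme.

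Two further inferences go beyond the text. It does not say that TAU participants complete the questionnaire at t2, so it cannot be asserted that they are asked about a programme they have not had; the article simply leaves open which arms answer. Nor does it give any figure for the direction or size of bias from non-response, so understatement of harm is a plausible risk and not a demonstrated result.

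Other information bears on safety. Anxiety, depression, alcohol use and quality of life are measured, and those who withdraw are asked why. These may signal deterioration, but they do not ask about negative effects of the programme. TAU crossovers receive the arm 2 programme, whose users are due to be asked at t2, so the intervention itself does not go unassessed. The full protocol may describe more safety reporting.

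What remains is a schedule the article itself fixes: one time point, placed before one arm's exposure, with no stated repeat.

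**Conclusion.** The point holds as a gap in a stated schedule. Up to 150 TAU crossovers, at most one third of those exposed, have no stated negative-effects measure after exposure. That finding does not depend on attrition or on which TAU access time applies; the upper figure assumes 150 per arm and that every TAU participant takes up the programme.

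The coverage figures are conditional. They range from 33% to 50% of exposed participants at 50% loss by t2, and from 44% to 67% at one-third loss. They assume equal loss across arms at t2, and they count everyone randomised to arm 1 or 2 as exposed, although the article expects low adherence. Data may therefore be missing for half or more of those exposed, but this is not certain.

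Neither the primary outcome nor the randomised comparison is affected. The change is worth making because it improves the harm data at very little cost.

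**What to change.** - Repeat the same questionnaire at t3, at minimum for TAU participants who have had access to the programme.
- Give it at t1 in arms 1 and 2, when the programme ends.
- Add it to the short set of questions put to participants who withdraw.
- State which arms answer it at t2 and, if TAU is included, how answers given before exposure will be interpreted.
- Reconcile the three statements of when TAU participants gain access, since they determine how much exposure a t3 questionnaire would cover.
- Report the number asked and the number answering, by arm and time point, beside the results.

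The cost is a few extra minutes of an existing online form at assessments already planned, with a slight increase in participant burden. No new visits are needed.
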